##### Game consoles and applications owned (T_0_, T_1m_, T_4m_, T_10m_)

At all measurements we assess which game consoles and game application the adolescents have access to in their home.

##### Game companions for active/non-active gaming (T_10m_)

At T_10m_ we assess with whom the adolescents usually play active and non-active games.

##### Process evaluation measures

A comprehensive process evaluation is conducted in the intervention group at T_1m_, T_4m_, T_10m_. Findings from focus groups and a survey about active and non-active gaming in adolescents provided a rationale for evaluating the following six elements [19,22]: 1) adherence to the intervention (usage of Move games, reasons for not playing at least one hour per week), 2) opinion of the Move games and the intervention (enjoyment, most played Move game, most enjoying Move game, ease of use, perceived competence, perceived physical exertion of playing Move games, opinion on the amount of provided Move games, self purchased Move game), 3) Game context (Move game companions, location of PlayStation Move console), 4) potential adverse effects (occurrence of injuries because of playing with the Move games), 5) activity replacement and 6) intention to continue playing the Move games. Table 3 shows all the process evaluation concepts, the items and answering categories as assessed in the questionnaire.

In addition to the questionnaires, adolescents’ time spent playing the active Move games in the intervention group is assessed on a daily basis over the whole 10-month period using a calendar format. The adolescents are asked to report type of Move game and amount of hours and minutes spent playing the Move games, according to Chinapaw et al. [41].

### Statistical analyses

First descriptive analyses are performed and data are checked for a normal distribution. Subsequently, control group and intervention group are described on baseline for demographics and outcome measures. Next, the effects of the intervention on all outcomes are evaluated by multilevel analyses. In the primary analyses, we analyze those participants which have at least one follow-up measurement in the groups they were randomized to. As a sensitivity analyses we will also impute follow-up measurements for persons with only a baseline measurement using multiple imputation with chained equations (intention to treat). Two models are constructed for each outcome measure: *model 1* adjusts for the baseline value of the outcome measure; and *model 2* additionally adjusts for demographics (age, sex, ethnicity and adolescent educational level) that are expected to associate with the outcome [3-5]. Second, analyses are performed according to the per protocol principle including the participants in the intervention group who played the Move games at least one hour per week. Adherence to protocol will be defined for each follow-up measurement separately, based on the question in the questionnaire assessing use of Move games (in hours per week) at T_1m_, T_4m_ and T_10m_. Again, two models are constructed for each outcome measure: *model 1* adjusts for baseline outcome measure; and *model 2* adjusts for demographics (age, sex, ethnicity and adolescent educational level) that are expected to associate with the outcome [3-5].

Additionally, a sensitivity analyses is performed by constructing all the models excluding the more extreme values on sedentary screen time (e.g. > 12 hours per day of non-active time). Further, if feasible (i.e. if the number of participants allows), explorative analyses are performed to check whether sex, age, adolescent educational level and ethnicity are effect modifiers, using a significance level of 0.10 because the study is not powered for detecting effect modification.

For the process evaluation, descriptive statistics are used describing the use of the Move games based on the Move game calendar over the ten months intervention period and the process evaluation measures. All statistical analyses are performed using IBM SPSS Statistics version 21 and statistical significance level is set at p < 0.05 for detecting main intervention effects and p < 0.10 for detecting effect modifiers.

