** *Process evaluation (only in intervention group)* **				
**1) Adherence to the intervention**				
Usage of Move games		x	x	x
Reasons for not playing (the minimal of one hour per week)		x	x	x

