**1) Adherence to the intervention**		
Usage of Move games	*Did you succeed in playing the move games for at least one hour per week?*	Specifically developed for the current study^1^
	-* Yes, I played the move games for at least one hour per week*	
	- *No, In some weeks I failed to play the move games for at least one hour*	
	- *No, I never succeed in playing the move games for at least one hour per week*	
Reasons for not playing (the minimal of one hour per week)	*Why did you not managed to play the move games for at least one hour per week?*	Specifically developed for the current study^1^
	- *I was too hot*	
	- *I was not allowed by my parents*	
	- *There was somebody else playing on the Move.*	
	- *The move console did not worked properly*	
	- *The move games did not respond well to my movements*	
	- *I think the move games are too tiring*	
	- *I think the move games are boring*	
	- *We have not enough space to play to move games well*	
	- *I had not enough move games*	
	- *I did not have time*	
	- *I think the move games are stupid*	
	- *I had to many other things to do*	
	- *There wasn’t somebody to play with and it is boring to play the games by myself*	
	- *I was injured*	
	- *I rather play non active games*	
	- *Other, namely …*	

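### The secondary per-protocol comparison filters only the intervention arm and is open to selection bias of unknown size and direction; separately, its adherence question does not yield the hours per week claimed for it

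*Protocol article*

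**What the plan says.** The primary analysis in the Statistical analyses section keeps adolescents with at least one follow-up measurement in their randomised groups. Multiple imputation for those with only a baseline measurement serves as a sensitivity analysis. A second, per-protocol analysis follows, "including the participants in the intervention group who played the Move games at least one hour per week". No restriction on controls is stated.

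On timing, the section says "Adherence to protocol will be defined for each follow-up measurement separately". The source is given as "based on the question in the questionnaire assessing use of Move games (in hours per week"), at one, four and ten months. Model 1 "adjusts for baseline outcome measure"; model 2 uses age, sex, ethnicity and educational level.

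The Move-use item in Table 3, under Adherence to the intervention, reads "Did you succeed in playing the move games for at least one hour per week". It offers three answers: yes; "No, In some weeks I failed to play the move games for at least one hour"; and never. Table 1 places it under "Process evaluation (only in intervention group").

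The section on process evaluation measures adds that Move playing time in the intervention group "is assessed on a daily basis over the whole 10-month period using a calendar format", in hours and minutes. The Statistical analyses section uses that calendar only to describe play.

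**The concern.** There are two separate problems, and they have different consequences.

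The first is selection. Whether an adolescent keeps playing is decided after randomisation and may go with motivation, taste for exertion or habitual activity. Table 3's own reasons for not playing include finding the games too tiring and preferring non-active games. Adherers may therefore differ in prognosis from the arm they came from, while controls stay unselected. The baseline outcome and four demographics do not capture motivation, baseline gaming or baseline physical activity.

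The second is measurement. The analysis section relies on a quantity that the listed question does not collect. That misclassifies adherence and leaves a coding decision open that could be taken after the data are seen. It does not by itself cause confounding.

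At stake is how a per-protocol result would be read. The section calls the effect-modifier analyses exploratory but gives the per-protocol analysis no such label. A positive result alongside a null primary analysis could be taken as evidence that an hour a week works.

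**Working it through.** The protocol gives no figure for this analysis to reproduce. The check is mainly textual, followed by an illustration of scale.

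**Who is compared with whom**
- Intervention arm: only those meeting the one-hour threshold (Statistical analyses).
- Control arm: no filter stated. The Move-use item is asked only in the intervention group (Table 1), so no matching filter could be applied. That all controls are kept is an inference, but no other reading fits.

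**What measures adherence**

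| Source | What it yields | Use in the plan |
|---|---|---|
| Question as described in Statistical analyses | Move use in hours per week | Defines the per-protocol set |
| Move-use item in Table 3 | Three answers, no hours, no recall period | The only Move-use question listed |
| Active-gaming items (section on time spent gaming) | Hours per week, all active games together | Outcome |
| Calendar (Process evaluation measures) | Hours and minutes of Move play, daily | Description only |

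The question as described matches none of the listed items. The middle answer in Table 3 covers anything from one missed week to nearly all weeks missed. An adolescent averaging well over an hour could give that answer, and the plan does not say how it is classified.

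**Illustration of scale under no treatment effect**

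Inputs from the sample-size section: target 0.5 kg, SD 1.5 kg, ICC 0.7, 119 recruited per arm, 20% drop-out. Analysed per arm: 119 × 0.8 = 95. Variance factor for the mean of two follow-ups: (1 + 0.7)/2 = 0.85.

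Assumed, because the protocol gives neither: the adherent share p, and the correlation r between adherence propensity and lower weight gain. With φ(c) the normal density at the cut-off leaving a share p above it:
- Spurious shift = r × φ(c)/p × 1.5 kg
- SE = 1.5 × √[0.85 × (1/(95p) + 1/95)]

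For p = 0.5, φ(c)/p = 0.399/0.5 = 0.798 and SE = 0.246 kg. With r = 0.1 the shift is 0.1 × 0.798 × 1.5 = 0.12 kg. The two-sided false-positive rate is P(Z > 1.96 − 0.49) + P(Z < −1.96 − 0.49) = 7.8%.

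For p = 0.3, φ(c)/p = 0.348/0.3 = 1.159 and SE = 0.295 kg.

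| p | r | Shift (kg) | Share of 0.5 kg | False-positive rate |
|---|---|---|---|---|
| 0.5 | 0.1 | 0.12 | 24% | 7.8% |
| 0.5 | 0.2 | 0.24 | 48% | 16.4% |
| 0.5 | 0.3 | 0.36 | 72% | 30.9% |
| 0.3 | 0.1 | 0.17 | 35% | 9.1% |
| 0.3 | 0.3 | 0.52 | 104% | 42.3% |

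A second parameterisation assumes a gap g in weight gain between adherers and non-adherers, so that shift = (1 − p) × g. It takes 99 analysed per arm and an effective SD of 1.256 kg, chosen so that 99 per arm gives 80% power at 0.5 kg. With g = 0.3 kg and p = 0.3, 0.5 and 0.7, the shift is 0.21, 0.15 and 0.09 kg and the false-positive rate 12.6%, 10.5% and 7.4%. With g = 0.75 kg it is 0.53, 0.38 and 0.23 kg, and 52%, 40% and 21%.

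If r or g has the opposite sign, the shift has the same size but counts against the intervention.

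**The case against.** The analysis is explicitly second to an as-randomised comparison, and all three hypotheses contrast intervention with control, not adherers with control. A secondary per-protocol analysis is conventional. Nothing in the protocol says it would override a null primary result. This stands and limits the weight of the point.

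A reader might infer that the per-protocol effect is shown to be biased in favour of the intervention. The protocol does not support that. It gives no adherence share and no relation between adherence and weight gain. The opposite sign is conceivable: keen gamers may adhere best, and the Discussion itself worries that active play may displace sport or cycling. The illustration is also in kilograms, whereas the primary outcomes are BMI-SDS, waist-SDS, hip circumference and skinfolds.

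A reader might also infer that the ten-month answer reflects only recent play and so misclassifies a measure built up over ten months. No recall period is stated, and the answers are worded over a span of weeks, so such a mismatch is not shown. Nor does the plan say that missing some weeks counts as non-adherence. Coding it so would be compatible with the weekly target, but the choice is not fixed.

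Item coding may be set out in a fuller document. That would settle the middle answer, but the article would still describe the question in terms its own table contradicts.

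**Conclusion.** The point holds as two moderate ones. The per-protocol contrast sets self-selected adherers against, by implication, all controls with thin adjustment. It is therefore open to selection bias of unknown size and direction. The 0.12 to 0.52 kg shifts and 8% to 42% error rates depend wholly on the assumed adherence (30% to 50%) and correlation (0.1 to 0.3). They show that modest selection could matter against a 0.5 kg target, not that it will occur.

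Independently of those assumptions, the description of the adherence question conflicts with Table 3, which means misclassification and an unfixed coding rule. The primary as-randomised analysis is untouched by either.

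**What to change.** 1. Correct the description of the Table 3 item in the Statistical analyses section.
2. Define adherence from the calendar already being collected: mean Move play of at least one hour per week from baseline to the visit concerned. Keep the Table 3 item, with a stated coding of its middle answer, as fallback or sensitivity check.
3. Label the adherer-versus-control contrast exploratory and non-causal.
4. Add, as a supplement, a complier-average causal effect with randomisation as instrument (two-stage least squares), adjusted for the model 2 covariates.

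The cost is a little more analysis and a wider interval for the complier estimate. Ten months of daily self-report may be incomplete. The complier estimate assumes that assignment has no effect below the threshold, which is open to doubt because every intervention family receives games, two controllers and encouragement. The threshold should be varied to check this. For that reason the estimate should accompany the labelled per-protocol analysis and not replace it.

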## Discussion

This paper describes the design of a trial to test the effects of a family oriented active game intervention on anthropometrics and self-reported behavior among adolescents. As mentioned in the introduction, the current trial on active games contributes to existing literature because it is one of the few adequately powered trials, includes normal weight adolescents, has a relatively long follow up period (ten months) and includes a comprehensive process evaluation. Further, the intervention uses the newest generation of active games and incorporates several motivational elements to encourage (maintenance of) active game play. Several studies have focused on overweight/obese children and showed that an active gaming intervention can result in small effects on BMI or body weight [35,60]. However, as far as we know the current trial is the first well powered RCT including normal weight adolescents. Furthermore, the comprehensive process evaluation will provide important insight into whether adolescents adhere to the active game intervention over a ten month period, whether they enjoy playing active games and the factors that hinder or encourage them to play the active games. This information can help to make future active game interventions more effective.

For the current study we chose to encourage the adolescents in the intervention group to substitute non-active gaming with active gaming as much as possible but at least one hour per week. The potential contribution of active games on prevention of excessive weight gain in adolescents, lies partly in the fact that adolescents are intrinsically motivated to play video games and active game interventions capitalize on this intrinsic motivation. As stated before behavior change is more likely to be maintained if one is intrinsically motivated, which means that one enacts in an activity because of the activity itself, because one enjoys the activity and not because of external factors [25]. Giving adolescents an encouragement to play the active games a minimum amount of time might conflict with this potential intrinsic motivation for active game play. However, it is suggested that only providing active games is not enough to impact physical activity or body weight and it is important to also give an instruction regarding the use of the active games [46,48].

The encouragement for the intervention group to replace at least one hour per week of non-active gaming with active gaming, is based on calculations in adults demonstrating that excessive weight gain can be prevented if the energy balance is affected by 70 kcal per week. This was the best estimation that could be made when designing the study, because no child specific equation was available at that time. Recently, Hall et al. [61] developed and validated a model that quantifies the energy imbalance underlying excess bodyweight in children and calculates the necessary intervention magnitude to achieve bodyweight change in children. This model shows that around 116 extra kcal per week should be expended to prevent an excessive weight gain of 0.5 kg in children with an average age of 14 years old. As studies have shown that active gaming can elicit an energy expenditure of 381 kcal [23], one hour of active gaming (assuming it does not replace more vigorous activities such as sports) should in theory be sufficient to prevent excess weight gain in children.

A concern regarding promoting active game play is that active game play might replace traditional forms of physical activity (e.g. cycling, playing outside) because these activities elicit greater energy expenditure and may therefore contribute more to prevention of excessive weight gain than active gaming. In a descriptive Dutch study among active gaming adolescents and their parents, adolescents reported that they thought active gaming had replaced sedentary activities [45]. However, this was asked in retrospect after adolescents were already playing active games, and recall bias might have occurred. To get more insight in whether stimulating active gaming will lead to replacement of sedentary activities or whether it takes adolescents away from physical activities in which they already participate, the current study also evaluates the effect of providing active games on sedentary behavior and physical activity.

The present study is subject to some limitations that need to be acknowledged. Although we obtain the primary outcome measures objectively (e.g. adolescents’ height, weight, waist/hip circumference and skinfolds), the secondary outcome measures (e.g. adolescents’ physical activity, sedentary behavior, consumption of snacks and sugar-sweetened beverages) are self-reported and thus liable to social desirability and recall bias. However, this will occur in both groups resulting in potential bias towards the null.

In conclusion, this trial will provide important new information on the potential contribution of active games to the prevention of excessive weight gain in adolescents and the process evaluation will provide relevant information for future active games studies on factors hindering or promoting active game play.
